### Recruitment

Study enrolment will be offered during the usual nursing practice, when eligible patients attend for follow-up wound care. They will be sequentially recruited upon signing the consent form.

#### Interventions

The **control group** will receive the usual treatment following the recommendations for the treatment of skin ulcers of the Madrid Health Service [1], which consists of assessment, cleansing, antisepsis, debridement, topical treatment (healing in a moist environment through the use of dressings) and multilayer compression therapy.

The **intervention group** will receive the usual treatment together with the “Active Legs” intervention, which consists of an evidence-based, structured, nurse-led educational intervention in health centre consultations. It incorporates a home-based lower limb exercise program and daily ambulation guidelines. Figure 1 shows schematically the different components of both the control and the Active Legs interventions. The home lower limb exercise program consists of four exercises of progressive difficulty, which the patient will perform twice a day, at least 5 days a week. In addition, patients will be required to follow a program of progressive daily ambulation until the target of 150 min/week (30 minutes for 5 days a week) is reached [25]. The detailed intervention is described using TIDieR (see Additional file 2).

**Fig. 1 Fig1:**
[figure not shown]
Components of Active Legs complex intervention vs standard clinical practice

Patients will be provided with an “Active Legs” diary containing all the information on the exercise program and a pedometer to record daily steps.

Those who have not reached complete healing at the end of the study will continue with the same treatment until complete healing is achieved and may resume the daily ambulation and exercise program.

In order to avoid possible differences in the application of the Active Legs program, training has been planned beforehand for the nursing professionals participating in the study, including both training in injury assessment and educational intervention.

### Outcomes

**The primary outcome** will be complete healing at 3 months follow-up: (yes/no), where complete healing is defined as complete epithelialisation maintained for at least 2 weeks and the time (in days) between the start of the study and complete wound healing.

**Secondary variables** are defined as complete healing at 6 months follow-up (yes/no), the degree of healing (Resvech 2. 0) which consists of 6 dimensions (depth, size, edges, wound bed, exudate and signs and symptoms of infection) with ascending scoring scales based on the severity of the dimension studied and a total score ranging from 0 to 35 [26]; the ulcer area (cm2), measured by digital photography and subsequent image processing using the open source Java image processing program “The ImageJ ecosystem” [27]; the VAS scale for perceived pain [28]; the level of adherence to the “Active Legs” intervention measured by the combined variable number of steps and time by means of the pedometer record (Yamax PZ270) and patients’ self-reported information on the home exercise program by means of the activity diary and the health-related quality of life measured with the CCVUQ-e, a questionnaire which in addition to an overall synthetic quality of life score, assesses the following dimensions: pain, depression, social relationships, impairment in performing activities of daily living and body image, with a score of 22 to 112 [29].

**Variables related to the healing process** are defined as Body Mass Index (kg/cm2); baseline pathology, diabetes mellitus (yes/no); last glycosylated haemoglobin (HbA1) value in the EHR; ABI score; tobacco and alcohol consumption; topical treatments used in existing ulcers; systemic treatments; adherence to multilayer compression therapy (yes/no); and physical activity level measured by the Minnesota Leisure Time Physical Activity Questionnaire, short version [30] and type of daily ambulation.

**Prognostic variables** are defined as location of the ulcer at the time of the study, number of ulcers at the time of the study, time (in days) of evolution of the venous ulcers before inclusion in the study and whether they are recurrent ulcers (yes/no).

**Variables related to recurrence (measured at 6 months follow-up)** are defined as occurrence of recurrence (yes/no), use of compression stockings (yes/no), light/normal/strong compression and hydration of the legs (yes/no).

**Additionally, data such as age, sex,** living alone (yes/no), employment status and level of education are collected.

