### Secondary objectives

To determine whether the Active Legs intervention produces better results than the standard practice on the rate of venous ulcers with complete healing at 6 months follow-up, the degree of healing achieved, the number of recurrences, the quality of life and the pain, as well as to describe the degree of adherence to and satisfaction with the intervention.

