### Sample size

Previous studies have obtained 50% complete healing rates at 12 weeks follow-up. Sample size has been calculated considering a relevant post-intervention average difference of 20% of complete healing between the intervention and control groups. Assuming an alpha error of 0.05 and a beta error of 0.02, 93 patients are necessary for each group. Expecting a 20% loss to follow-up after a 3-month period, the required sample size is 224 patients (112 per group).

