### Analysis

A descriptive analysis (means, medians, frequencies of distribution) will be performed. The results for the primary outcomes will be analysed on an intention-to-treat (ITT) basis. To analyse the principal effectiveness the incidence rates of completely healed ulcers will be compared with their point estimate and 95% confidence interval. Time to complete healing will be compared using Kaplan-Meier curves (Log-rank test). A Cox regression model will be used to adjust for prognostic factors.

To analyse secondary outcomes, an explanatory model will be fitted with linear or logistic analysis, as appropriate.

Significance will be set at *p* < 0.05. All analyses will be performed using STATA software.

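### Recurrence (yes/no) at a fixed 6 months is confounded with healing: it tends to count against the arm that heals more and sooner, even if recurrence itself is unaffected.

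*Protocol article*

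**What the plan says.** - **Objective.** Under Secondary objectives, the protocol article asks whether Active Legs does better than standard practice on several outcomes, among them "the number of recurrences".
- **Variable.** Under Outcomes, the recurrence block lists "occurrence of recurrence (yes/no"), read at the 6-month follow-up. That time point runs from study start, not from healing.
- **Analysis.** The Analysis section states: "To analyse secondary outcomes, an explanatory model will be fitted with linear or logistic analysis, as appropriate". Kaplan-Meier, log-rank and Cox methods are named only for time to complete healing. Intention-to-treat is stated for the primary outcomes only, so the denominator for recurrence is open.
- **Visits.** Under Data collection methods, data are collected every 14 days for 3 months (or until earlier healing) and then once at 6 months. No date of recurrence is listed.
- **Related outcome.** Complete healing at 6 months (yes/no) is a secondary variable. The article does not say how a patient who healed and then recurred counts in it.

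**The concern.** A patient cannot have a recurrence before the ulcer has closed. The trial is designed to find more healing in the intervention arm and also measures how soon healing occurs. If its hypothesis is right, that arm has more patients who can recur, and each has had longer to do so by month 6.

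A yes/no comparison at that date mixes recurrence with healing, whichever denominator is used:

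- **All randomised.** An unhealed patient counts as having no recurrence, so failure to heal is scored as a good result.
- **Healed patients only.** The groups are selected after randomisation and have unequal time at risk.

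A logistic or linear model on the yes/no variable removes neither problem. At stake is a misleading pair of results, better healing alongside apparently more recurrence, on an outcome the protocol names as an efficacy objective.

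**Working it through.** **Inputs from the protocol (Sample size).** "Previous studies have obtained 50% complete healing rates at 12 weeks follow-up", and a "relevant post-intervention average difference of 20% of complete healing between the intervention and control groups". I read this as 50% versus 70% healed at 3 months, with 112 per arm.

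**Check of that reading against the plan's own figure.** With two-sided alpha 0.05 and power 0.80:

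n = [1.960·√(2·0.6·0.4) + 0.842·√(0.5·0.5 + 0.7·0.3)]² / 0.20² = (1.358 + 0.571)² / 0.04 ≈ 93 per group.

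This matches the stated 93, so the pair is the one used. The printed beta of 0.02 would give 190; that is a separate matter. The protocol states no figure for recurrence, so there is none to reproduce.

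**Assumptions, not in the protocol.** Healing is exponential and continues at the same rate to month 6. The recurrence hazard r after healing is constant and *identical* in both arms, at 2%, 5% or 8% per month. Dropout and the 2-week confirmation of healing are ignored.

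**Step 1, healing.** The hazard is h = −ln(1 − p)/3, the proportion healed by month 6 is H = 1 − e^(−6h), and the mean time from healing to month 6 is (6 − H/h)/H.

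- Control: h = 0.231; H = 75%; mean time 3.67 months.
- Intervention: h = 0.401; H = 91%; mean time 4.10 months.

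**Step 2, recurrence by month 6 per randomised patient.** R = H − h·(e^(−6r) − e^(−6h))/(h − r). At r = 0.05:

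- Control: 0.75 − 0.231·(0.741 − 0.25)/0.181 = 0.124, about 14 of 112.
- Intervention: 0.91 − 0.401·(0.741 − 0.09)/0.351 = 0.167, about 19 of 112.

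Among the healed, R/H is 16.5% versus 18.3%.

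**Step 3, range.**

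| Hazard per month | All randomised, control vs intervention | Ratio | Among healed | Ratio |
|---|---|---|---|---|
| 2% | 5.3% vs 7.1% | 1.35 | 7.0% vs 7.8% | 1.11 |
| 5% | 12.4% vs 16.7% | 1.35 | 16.5% vs 18.3% | 1.11 |
| 8% | 18.6% vs 25.0% | 1.34 | 24.8% vs 27.4% | 1.11 |

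Recurrences per person-month healed are equal in the two arms by construction, so the whole excess comes from numbers and time at risk.

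**Step 4, what would cancel it.** I solved for the recurrence hazard ratio that equalises the two arms, over a wider range of recurrence (3-month risk after healing of 5% to 30%). It is 0.69–0.73 with all randomised and 0.88–0.89 among the healed. These are true reductions of about 27–31% and 11–12%.

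**Step 5, chance of a nominally significant result against Active Legs (5% per month, no effect on recurrence).**

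- All randomised: difference 4.3 points, standard error 4.7, ratio 0.91; Φ(0.91 − 1.96) ≈ 15%.
- Among the healed (about 84 and 102 patients): difference 1.8 points, standard error 5.6, ratio 0.33; Φ(0.33 − 1.96) ≈ 5%.

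With no distortion the figure would be 2.5%.

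**The case against.** **The article is condensed.** The denominator and the definition of recurrence could sit in an analysis plan that is not shown. The sentence on linear or logistic models is generic, and recurrence stands in its own block rather than in the list of secondary variables. This has weight for the denominator, and I do not count its absence as an error. But the between-arm objective, the yes/no variable, the fixed 6-month reading and the model family are all stated, and the problem arises under either denominator.

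**Healed-only is a plausible reading.** The recurrence block also holds compression stockings and leg hydration, which read as aftercare for a closed ulcer. On that reading the distortion is modest: 1.8 points in the central case, and a significant wrong-direction result is unlikely. This stands. It does not remove the selection after randomisation, whose direction cannot be derived from the documents.

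**Over all randomised patients the contrast is a valid randomised comparison.** As a total effect, that is correct. But it does not answer whether recurrence is reduced, because less healing lowers the count.

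**The size rests on assumptions.** The protocol gives no usable recurrence hazard and no 6-month healing rate. Its Background cites a mean ulcer duration of 10.7 months with a spread of 27, which suggests a longer tail than a constant healing hazard. This stands for the percentages. Within the model, the ratios hardly change with the recurrence hazard.

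**Conclusion.** The point holds as a tendency, not a certainty. The planned comparison is confounded with healing and leans against Active Legs when it improves healing. If recurrence itself is unaffected, the apparent excess is about 1.34- to 1.35-fold over all randomised patients and about 1.11-fold among the healed. These figures assume exponential healing at 50% versus 70% by 3 months and equal constant recurrence hazards.

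A reader might infer that an effective intervention would necessarily appear to cause more recurrences. The documents do not support that. The protocol's rationale is that exercise acts on the underlying venous cause, so a protective effect on recurrence is possible. One larger than about 27–31% (all randomised) or 11–12% (healed only) would still show as fewer recurrences, though understated. Nor do the documents say that unhealed patients count as free of recurrence, so the larger ratio cannot be taken as the plan's own.

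The matter concerns one secondary objective and does not touch the primary result. It is still worth correcting.

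**What to change.** 1. For this objective, make the between-arm comparison ulcer-free status at 6 months, meaning healed and not recurred, in all randomised patients. It keeps the randomised groups, and less healing can no longer look like an advantage. In the central scenario it gives 75.0 − 12.4 = 62.6% versus 91.0 − 16.7 = 74.3%, if no recurred ulcer heals again.
2. State how this relates to complete healing at 6 months. The two overlap, and the new definition settles how a healed-then-recurred patient counts.
3. Report recurrence among healed patients descriptively, by arm and with time since healing, and say that it is not a randomised comparison.

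**Cost.** Item 1 uses data already collected (healing, 6-month status, recurrence) and needs only a change of wording. A rate per person-month under item 3 needs more, because no visit is scheduled between 3 and 6 months and no recurrence date is listed. Either add a field at the 6-month visit for the dates of recurrence and of any healing after month 3, or treat those dates as interval-censored.

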### Participant timeline

Table 1 shows the participant timeline.

**Table 1 Tab1:**
[figure not shown]
Participant timeline

^a^Until complete healing of the wound

^b^Intervention group only

### Data collection methods

Patient information will be obtained through clinical interviews, electronic medical records and wound examination in the nursing consultation of the professionals participating in the study. The same information will be collected from participants in the control and intervention groups, except for the level of satisfaction and adherence. Data will be collected every 14 days for the first 3 months or sooner if the ulcers have healed, and at 6 months follow-up.

Patients who refuse to participate in the study, losses and dropouts and their cause, as well as patients who are required to drop out because of withdrawal criteria, will be recorded.

### Data management

The information will be recorded in an electronic data collection notebook designed for the study, which contains all the questionnaires and scales, collected in the variables section, for implementation. Photographs of ulcers will be temporarily stored in the electronic notebook until the ulcer area is measured.

### Losses in participation

Losses and dropouts during the study and their cause, as well as patients who are required to drop out because of withdrawal criteria, will be recorded. In order to minimise potential losses, as a method of encouraging participation, patients and/or carers will be contacted by telephone to arrange visits.

In the event of dropouts during follow-up, at least 2 telephone calls will be made to record their cause.

### Analysis

A descriptive analysis (means, medians, frequencies of distribution) will be performed. The results for the primary outcomes will be analysed on an intention-to-treat (ITT) basis. To analyse the principal effectiveness the incidence rates of completely healed ulcers will be compared with their point estimate and 95% confidence interval. Time to complete healing will be compared using Kaplan-Meier curves (Log-rank test). A Cox regression model will be used to adjust for prognostic factors.

To analyse secondary outcomes, an explanatory model will be fitted with linear or logistic analysis, as appropriate.

Significance will be set at *p* < 0.05. All analyses will be performed using STATA software.

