**Methods:**

A randomized, multicentre clinical trial. A total of 224 individuals receiving primary nursing care with a diagnosis of venous ulcer, with a diameter of 1 cm or greater and an ankle-brachial index between 0.8 and 1.3, able to comply with the study requirements and consenting to participate, will be sequentially included (112 per group).

Both groups will receive the standard treatment in primary care, with cleansing, debridement and healing in a moist environment together with multilayer compression therapy. The intervention group will also receive a structured educational intervention involving lower limb physical exercise and daily ambulation guidelines.

The primary response variables will be complete healing –understood as complete and sustained epithelialisation for at least 2 weeks– and time to healing. The secondary variables will be degree of healing, ulcer area, quality of life, pain and variables related to the healing process, prognosis, and recurrences. Sociodemographic variables, adherence to treatment and satisfaction variables will also be recorded. Data will be collected at baseline, at 3 months and at 6 months follow-up. Survival analysis (Kaplan-Meier and Cox) will be performed to measure primary effectiveness. Intention-to-treat analysis.

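### The article names two different primary analyses, and makes both healing and time to healing primary at one 0.05 level with no order between them

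*Protocol article*

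**What the plan says.** The statements on the primary comparison, by section of the protocol article:

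- **Abstract, Methods.** Complete healing and time to healing are both primary response variables. On method: "Survival analysis (Kaplan-Meier and Cox) will be performed to measure primary effectiveness".
- **Main objective.** The question is the rate of complete healing at 3 months; time to healing is not mentioned.
- **Sample size.** The calculation uses the healed proportion only (50%, with a 20-point difference) and counts patients: "93 patients are necessary for each group".
- **Outcomes.** Of the main endpoint, this section says that it "will be complete healing at 3 months follow-up: (yes/no), where complete healing is defined as complete epithelialisation maintained for at least 2 weeks". The same sentence adds "the time (in days) between the start of the study and complete wound healing", with no end point for the follow-up that counts.
- **Analysis.** "To analyse the principal effectiveness the incidence rates of completely healed ulcers will be compared with their point estimate and 95% confidence interval". Then: "Time to complete healing will be compared using Kaplan-Meier curves (Log-rank test". An adjusted Cox model follows. The section speaks of primary outcomes in the plural and sets one significance level, 0.05, for everything.
- **Unit.** Participants are allocated. Outcomes lists "number of ulcers at the time of the study" among the prognostic variables, so a patient may have more than one. The article gives no rule for classifying such a patient as healed or not healed.

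**The concern.** The abstract and the Analysis section attach the primary claim to different methods, and the Outcomes sentence joins both endpoints under one primary outcome. If the two tests fall on opposite sides of 0.05, the article can be cited for either conclusion. If a positive result on either one counts as success, the overall false-positive rate is above 5%. The trial is open-label and healing is recorded by unmasked nurses, so a primary analysis fixed in advance is one of the main safeguards available.

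A smaller wording issue sits in the same sentence. The comparison is phrased in healed ulcers, while patients are randomised and counted in the sample size. For a patient with one healed and one open ulcer, the yes/no outcome has no stated value.

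**Working it through.** **1. Which endpoint the sample size supports.** Inputs from Sample size: p1 = 0.50, p2 = 0.70, alpha 0.05 (two-sided assumed). With mean proportion 0.60:

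n = [1.960·√(2·0.60·0.40) + z(power)·√(0.50·0.50 + 0.70·0.30)]² / 0.20²

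- Power 0.80: (1.960·0.6928 + 0.8416·0.6782)² / 0.04 = (1.3579 + 0.5708)² / 0.04 ≈ 93.0, the article's 93.
- The printed beta of 0.02 (power 0.98): (1.3579 + 2.0537·0.6782)² / 0.04 ≈ 189.2, or 190 per group. The printed beta therefore does not give 93, whereas 0.20 does. That is a separate point.

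The 93 is thus the size for one two-sided comparison of proportions at the full 0.05. Nothing in it provides for a second primary test.

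**2. False-positive rate if either test may win.** Simulated under no effect: 50% healed by day 84 in both arms, exponential healing times, healing seen on a 14-day grid, 20,000 trials per row (Monte Carlo standard error about 0.2 points). The tests are the pooled two-proportion test at day 84 and the log-rank test.

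| Per arm | Log-rank horizon | Either p < 0.05 | Correlation of the two z statistics |
|---|---|---|---|
| 93, no losses | day 84 | 5.7% | 0.98 |
| 93, no losses | day 182 | 7.8% | 0.79 |
| 112, 20% dropout | day 84 | 6.2% | 0.95 |
| 112, 20% dropout | day 182 | 8.0% | 0.77 |

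Each test alone stays at 4.7% to 5.1%. Independent tests would give 1 − 0.95² = 9.75%. The excess is smaller because both tests use the same healing events.

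**3. How often the tests disagree at 50% versus 70%.** With 112 per arm, no losses and log-rank to 3 months, one run gave: proportions significant 0.866, log-rank 0.893, either 0.906. Both significant = 0.866 + 0.893 − 0.906 = 0.853, so exactly one = 0.906 − 0.853 = 0.053. A repeat with 40,000 trials gave 0.866, 0.890 and 0.902, so exactly one = 2·0.902 − 0.866 − 0.890 = 0.048. Disagreement at the 3-month horizon is therefore about 5% to 6%. It rises to about 15% with 93 per arm and log-rank to 6 months.

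**4. What control would cost.** One named primary test keeps alpha at 0.05 and 93 per group (power 80.0%). Keeping both as alternative primaries at 0.025 each needs 113 analysed per group for the proportion, or 113 × 1.2 = 135.6, i.e. 136, with the article's own allowance for losses. With 93 analysed at 0.025, power is 71.0%.

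**The case against.** The strongest reply is that the body of the article leans one way. Main objective, Sample size and the sentence on principal effectiveness all point to the 3-month healing rate. Log-rank then reads as the method for the time component and Cox as adjustment, and an abstract is only a summary. Multiplicity rules are also often left to an analysis plan, which is not at hand, and the analysts are to be unaware of allocation.

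Much of this stands. The missing order or alpha split would be weak ground alone, and the lean of the body shows which way to resolve the matter. It does not remove the conflict. The abstract assigns primary effectiveness to survival analysis outright, and the Outcomes section, which is in the body, also makes time to healing primary.

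Two stronger readings do not stand.

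- A reader might infer that the plan lets success be claimed on either test, so that its error rate exceeds 5% as a matter of fact. No section states such a rule. The inflation is conditional on it and disappears if one test is named primary or both must succeed. The 8% also needs a log-rank test run to 6 months. The article does not rule this out, but the main objective is set at 3 months and 6-month healing is secondary.
- A reader might infer from the reference to healed ulcers that ulcers will be analysed as independent observations, with confidence intervals too narrow. The article never says so. The sample size counts patients, the outcome is a yes/no with wound in the singular, and number of ulcers is listed as a prognostic variable. The article gives neither ulcers per patient nor within-patient correlation, so any error figure would rest wholly on assumed inputs.

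**Conclusion.** The point holds as an inconsistency within the article about which analysis is primary, with two primary endpoints at one 0.05 level and no order. Its size is modest: about 6% instead of 5% if either test may win and log-rank stops at 3 months, and about 8% if it runs to 6 months. Disagreement at the design effect is roughly 5% to 15% across those horizons and sample sizes. These figures assume exponential healing, one outcome per patient and 14-day observation throughout, whereas Data collection methods gives 14-day visits only for the first 3 months. At the 3-month horizon the two tests are nearly the same test, so the practical harm is less the extra error than the freedom to choose when they differ. The ulcer wording supports only a clarification to patient level.

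**What to change.** - Make complete healing at 3 months, per randomised patient, the single primary outcome, analysed as a difference in proportions with its 95% confidence interval. This matches Main objective and Sample size.
- Make time to healing (log-rank, with Cox as the adjusted analysis), censored at 3 months, the first secondary outcome, with its log-rank test made at 0.05 only if the primary is significant. This holds the error over the two tests at 5%.
- Say the same in the abstract, Outcomes and Analysis.
- In Analysis, replace healed ulcers with patients healed, and state one patient-level rule for patients with several ulcers. A pre-specified index ulcer is one option; requiring all ulcers to heal is another.

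The cost is protocol wording, with the sample size unchanged. At 112 per arm with no losses, the chance of a positive claim falls from about 90% (either test, log-rank to 3 months) to about 87% (the proportion alone). Compared with a log-rank test run to 6 months, more would be given up if the benefit persisted. Naming time to healing as primary would also end the conflict, but Main objective and Sample size would then have to be rewritten.

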## Background

Ulcers of venous aetiology are lesions caused by a process of chronic venous insufficiency [1, 2], with a tendency to a torpid evolution, a low tendency to spontaneous healing [1, 3] and a high recurrence rate [4, 5]. For diagnosis, in addition to the presence of signs of chronic venous insufficiency, it is necessary to assess the ankle brachial index (ABI) [2].

In Spain, lower limb ulcers have a prevalence of 0.1 to 0.3% in the adult population [2] and an incidence of 3 to 5 new cases per thousand people annually (2.6), both values becoming twice as high in the over-65 population segment [2]. Venous ulcers (VU) account for 75–80% of all lower limb ulcers [2, 6] with an average duration of 10.7 months (+ − 27 months) and over 50% being recurrent ulcers [1, 2]. They represent 2.5% of primary care consultations and between 1.5 and 3% of total healthcare expenditure in neighbouring countries [1].

In clinical terms, ulcers of venous origin usually show signs such as high levels of exudate, malodour, moderate pain, and infection, causing sleep disturbances, mobility problems, decreased vitality and even dependence in performing basic activities of daily living [7–9]. A negative emotional impact and a low perceived quality of life have also been observed [10, 11].

There are two main components to ulcer treatment. On the one hand, the topical healing of the wound, favouring a moist environment through the use of dressings [1], and on the other hand, the control of chronic venous insufficiency through the use of compression therapy [1, 12].

Recent studies show that these patients suffer from muscle pump dysfunction of the lower limbs [13, 14], resulting in poorer healing rates [5] and decreased ankle mobility [15, 16] associated with a process of fibrosis involving the Achilles tendon [16].

The lack of competence of the muscle pump, together with the decreased ankle mobility and the age at which VUs are most prevalent (over 65 years) could be among the reasons why approximately 50% of patients suffering from VU have an insufficient level of physical activity (less than 10 min of ambulation per day), as suggested by various authors [5, 7, 13, 17].

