### Randomization and masking

Simple random allocation to one of the two study groups via the Electronic Data Collection Notebook.

It is not possible to mask the intervention in this type of trial, although the analysis will be performed by professionals who are unaware of the allocation.

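### Baseline ulcer area is not among the listed prognostic variables and the 3-month healed proportion is compared without covariates; adjusting for area in both primary analyses is a free improvement

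*Protocol article*

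**What the plan says.** **Prognostic variables (Outcomes).** They "are defined as location of the ulcer at the time of the study, number of ulcers at the time of the study", followed by time of evolution before inclusion and whether the ulcer is recurrent. Ulcer size is not in this list, nor in the separate list of variables related to the healing process.

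**Ulcer area (Outcomes).** It is listed as a secondary variable: "the ulcer area (cm2), measured by digital photography". The Abstract has data collected at baseline, 3 months and 6 months. Table 1 is not shown, so baseline measurement of area is inferred from these two places.

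**Eligibility (Setting and study population).** The lesion must be at least 1 cm in diameter. No upper limit is given.

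**Allocation (Randomization and masking).** "Simple random allocation to one of the two study groups", with no stratification or blocking mentioned.

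**Primary analyses (Analysis).** The healed proportions are compared by point estimate and 95% confidence interval, and time to healing by Kaplan-Meier curves and a log-rank test. No covariates are stated for either. Adjustment appears only in the next sentence: "A Cox regression model will be used to adjust for prognostic factors".

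**Sample size.** It is built on the healed proportion: "Previous studies have obtained 50% complete healing rates at 12 weeks follow-up", with a difference of 20 percentage points taken as relevant.

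**The concern.** A larger ulcer has more surface to close within the same 3 months, so initial size is a natural candidate predictor of complete closure. The range admitted is wide: for circular ulcers, going from 1 cm to an illustrative 5 cm in diameter multiplies the area by 25. The protocol's own healing scale, Resvech 2.0, also scores size as a severity dimension. A prognostic list without size sits awkwardly with all of this.

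Two things are at stake. The first is precision: a baseline variable that predicts healing can narrow the interval for the treatment difference, and this one appears to be collected anyway. The second is accuracy in the trial actually run: simple randomisation can by chance leave one arm with larger ulcers, and the planned comparison of healed proportions has no means of correcting for that. The Cox model can correct for imbalance in the factors it contains, but as listed these do not include size.

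**Working it through.** **1. The plan's own sample size.** Inputs from the Sample size section: 50% versus 70% healed (30% versus 50% gives the same answer) and alpha 0.05, taken as two-sided. With pooled variance and no continuity correction,

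n = [z(α/2)·√(2·p̄·q̄) + z(β)·√(p1q1 + p2q2)]² / Δ²

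With p̄ = 0.6 and beta 0.20: [1.960 × 0.6928 + 0.8416 × 0.6782]² / 0.04 = 93 per group. The printed beta of 0.02 would give 190, so 93 corresponds to 80% power. That misprint is a separate matter. The stated 112 per group is 93 × 1.20. After a 20% loss, 112 × 0.8 = 89.6 per group remain, with 78.5% power against 80.0% at 93. The calculation is thus for an unadjusted comparison of two proportions.

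**2. Gain by formula.** If baseline covariates explain a share R² of the outcome variance, the effective sample size is about n/(1 − R²). The same precision as 93 per group then needs 93 × (1 − R²): 89 at R² = 0.05, 84 at 0.10, 80 at 0.15 and 75 at 0.20.

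**3. Gain by simulation.** The documents give no prognostic strength for area, so a range is assumed: an odds ratio for healing of 1.5 to 3.0 per SD of log area, larger ulcers healing less often. Each scenario used 3,000 simulated trials of 186 analysed patients under simple randomisation, with true healing of 50% and 70%. Variances compare the raw risk difference with one standardised from a logistic model containing log area. Power compares the two-proportion test with the treatment test in that logistic model.

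| Odds ratio per SD | R² | Variance ratio, adjusted/unadjusted | Power, unadjusted | Power, adjusted | Gain (points) |
|---|---|---|---|---|---|
| 1.0 | 0.000 | 1.005 | 80.0% | 79.6% | nil |
| 1.5 | 0.035 | 0.973 | 81.4% | 82.5% | 1.1 |
| 2.0 | 0.093 | 0.915 | 79.6% | 82.9% | 3.3 |
| 2.5 | 0.145 | 0.854 | 79.4% | 84.9% | 5.5 |
| 3.0 | 0.190 | 0.815 | 79.4% | 87.9% | 8.5 |

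A repeat with 20,000 trials per scenario gave gains of 1.0, 3.1, 5.7 and 7.4 points for odds ratios 1.5 to 3.0. The gain is therefore about 1 to 8 points.

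**4. Chance imbalance.** The standardised difference in mean log area between arms has SD √(2/n): 0.147 with 93 per arm and 0.134 with 112. A difference above 0.25 SD in either direction has probability of about 9% and 6% respectively. In the 3,000-trial runs where the intervention arm had the larger ulcers by more than 0.25 SD, the mean unadjusted difference fell from the true 0.20 to 0.157 (odds ratio 2.0) or 0.133 (odds ratio 3.0). The adjusted estimate stayed at about 0.20.

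**5. Validity.** With no treatment effect, rejection rates were 4.7% to 5.5% unadjusted and 4.6% to 5.6% adjusted. Adjustment changes precision and conditional accuracy, not the type I error.

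**The case against.** The strongest reply is that the plan is coherent as written. The sample size reproduces from an unadjusted comparison of two proportions, the analysis makes that comparison, and an adjusted Cox model covers time to healing, the other part of the primary outcome. An unadjusted primary proportion under simple randomisation is a legitimate choice. This stands, so the point is an improvement and not the correction of an error.

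It can also be said that an article condenses the plan, that the Analysis section does not expressly tie its prognostic factors to the list under Outcomes, and that an analysis plan not shown could add area. This stands in part: the omission from the Cox model is an inference. But the protocol does define a set under that name, and area is not in it.

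The size of the gain rests on an assumption. This stands in full. The formula and simulation concern the proportion and were not repeated for the Cox model, where adding covariates also changes the hazard ratio being estimated.

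A reader might infer several stronger points, which the documents do not support:

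- *Duration enters the model in raw days and is dominated by a few very old ulcers.* Days are only the recording unit; no functional form is stated. The Background figure ("average duration of 10.7 months", with plus or minus 27 months) is never called an SD and describes venous ulcers in general, not this trial's patients.
- *The secondary models leave out the outcome's baseline value.* The text says only that "an explanatory model will be fitted with linear or logistic analysis, as appropriate". It names no covariates, so it excludes none.
- *The plan adjusts for compression adherence after randomisation.* That variable is listed with the healing process, not among the prognostic variables.
- *Uneven splits within the 16 centres damage the comparison.* Recruitment per centre is not stated, and such splits do not bias the overall comparison on average.

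**Conclusion.** The point holds as a free improvement. The protocol's prognostic list omits baseline ulcer area, its comparison of 3-month healing states no covariates, and its allocation does nothing to balance size. It would be wrong to conclude that the planned analysis is biased or has an inflated type I error; it is valid on average. What is lost is precision, and protection in the particular trial where size happens to be unbalanced.

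The size depends on how strongly area predicts healing: from about 1 point of power and 3% of variance at the weak end of the assumed range to about 8 points and 18% at the strong end, and nothing if area is not prognostic. From an odds ratio of 2.0 upwards, the gain exceeds the 1.5 points lost because losses were allowed for by multiplying by 1.2 (80.0% − 78.5%). All of this assumes that area is measured at baseline.

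**What to change.** Add log baseline ulcer area to the four prognostic variables already listed, keeping all four. Prespecify that one set for both primary analyses:

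- the Cox model for time to healing;
- a logistic model for complete healing at 3 months, reported as a standardised risk difference with 95% CI.

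Report the unadjusted proportions and log-rank result alongside, and state in advance that the adjusted results lead. Fixing the set beforehand also removes any choice of covariates after results are seen, which is worth having in an open-label trial.

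The model is affordable. At 50% and 70% healing with 93 per group, about 93 × 0.5 + 93 × 0.7 = 112 of 186 patients heal and 74 do not, enough for five prognostic variables if location is kept to a few categories.

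The cost is a change of wording in Outcomes and Analysis: no new data, patients or visits, provided area is recorded at baseline as the Abstract and Outcomes imply.
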